**Figure 1 F1:**
[figure not shown]
Experimental design diagram.

The sample size was determined by an a-priori power analysis using the G^*^Power3 software for Mac (72) following the indications of Beck (73). The effect size value used was: d = 0.70 with a total sample size of 30, based on a study of WB-EMS training on hip circumference in postmenopausal women (60), with two levels for the between-subject factor (EX+WB-EMS, EX), three levels for the within-subject factor (Baseline, 10 weeks, 6 months), alpha error probability set at 0.05 and a power of 0.80. This analysis indicated a minimum total sample size of 22 participants. Considering a dropout rate of 25%, 14 participants per arm will be required. In order to check the minimum effect size to which the model will be sensitive, a sensitivity analyses with the overestimated sample size assuming a 25% of dropout rate (*n* = 28) was done. The power and alpha values used were 0.80 and 0.05, respectively. The model will be sensitive enough to detect effects as small as d = 0.60.

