#### Physical Fitness

One of the evaluations of the physical performance will be carried out by the EXERNET test consisting of 8 tests modified and previously adapted from the “Senior Fitness Test Battery” and “Eurofit Testing Battery” (85).

1. Balance: “Flamingo test.” Participants will start standing, with both feet on the ground. After the signal, they will try to stand on the sole of one foot. The time the subject can stay in that posture up to a maximum of 60 s will be recorded. The test will be performed alternately, twice with each leg. The best attempt of the four will be registered.

2. Leg strength: “Chair Stand Test.” The participant will start from a sitting position with her arms crossed and the palms of her hands resting on her shoulders. The number of times she will be able to get up and sit in 30 s will be registered. The test will be performed only once.

3. Arm strength: “Arm Curl Test.” Participants will sit on a bench holding a 2.5-kg dumbbell. The maximum number of elbow's flexo-extension that the participant will be able to execute in 30 s will be registered. The test will be performed once with each arm.

4. Legs flexibility: “Chair Sit-and-Reach Test.” Participants will begin the test sitting, with one leg extended and the heel resting on the floor, while her hands will be directed toward the toes of that leg. The existing distance, positive or negative, in centimeters, between the fingers and toes will be registered. The test will be performed once with each leg.

5. Arms Flexibility: “Back Scratch Test.” The participant will place a hand over the shoulder of that same arm, and the opposite hand from the bottom up, trying to touch each other. The participant will try to touch or overlap the fingers of both hands. The distance in centimeters (positive or negative) between the fingertips of each hand will be registered. The test will be carried out twice, once with each arm.

6. Agility: “8-Foot Up-and-Go Test.” From a sitting position, the seconds that the participant will take to get up, walk to a cone located at 2.45 m, go around it, and sit down again will be registered. The test will be performed twice with at least 1-min rest between repetitions and the best result will be recorded.

7. Speed: “Brisk Walking Test.” The time taken for each participant to walk 30 m will be measured. Two repetitions will be performed with a minute of rest between them. The best of both results will be recorded.

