8. Cardiovascular resistance: “6-Min Walk Test.” In a circuit of 46 meters delimited by cones, the distance in meters that each participant will be able to cover walking for 6 min will be registered.

In addition to the mentioned evaluations, a progressive resistance test (PRT) (86) will be carried out to make a more accurate assessment of the strength development. The PRT permits simultaneous direct calculations of strength (N), velocity (m·s-1). and power (w), produced with different loads, and at the same time. Taking into account that as a consequence of aging, losses in strength are observed mostly in the type II fibers (87), the mean velocity and the mean power of exertion will be assessed in this study.

Following the PRT test protocol, we will assess the mentioned variables with the execution of 6 to 8 series of 2 to 3 repetitions in squat and bench press, applying the maximum acceleration possible, alternated with rest intervals of 2–5 min. The rest period is proportional to the intensity and duration of the effort, to avoid the prediction errors caused by the accumulated fatigue. The load will be increased progressively with the series. For each magnitude of weight lifted, it is necessary to select the repetition with which the highest values of average velocity and power are reached, as this factor expresses the highest mechanical efficiency of the exercise (88). In this study, the best repetition of the best series will be recorded. Then, the load in which that best series is done in the pre-test will be used in the post-test to compare the evolution of the variables after the intervention in the post-test 1 and the follow-up.

To perform this test a lineal encoder Chronojump® (Bosco–System, Barcelona, Spain) will be used in order to detect the position of the resistance during linear movements. This data permits an estimate of the range of movement, acceleration, velocity, strength and the power produced during each action (89).

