### Statistical Procedures

After checking normality and homogeneity assumptions, the effectiveness of different training programs on quantitative dependent variables will be assessed by a 2 × 2 mixed ANOVA. Group training intervention (“EX+WB-EMS,” “EX”) will be included as between-subjects factor, improvement (“10 weeks from Baseline,” “6 months from Baseline”) will be included as the repeated within-subjects factor, and group ^*^ improvement will be included to account for the interaction effects. Whenever a significant main effect or interaction will be observed, Bonferroni's *post hoc* correction will be used to aid interpretation of these main effects or interactions, either between-subjects factor at whatever time point or within-subjects factor at whatever group (102, 103). Hedge's *g* effect size (*g*) will be calculated and interpreted as follows *g* < 0.20 = trivial, *gfrom*0.20*to*0.50 = *mild, g* from 0.50 to 0.80 = moderate and *g* > 0.80 = large (104). Whenever the data fails to meet assumptions, robust methods will be performed following procedures of (105) and the explanatory measure of effect size (ξ) will be calculated and interpreted as suggested by (106). Values of ξ = 0.10, 0.30, and 0.50 correspond to small, medium, and large effect sizes, respectively. The qualitative ordinal variables will be analyzed with a 2 × 2 rank-based ANOVA following directions from (107). Significance level will be set at α= 0.05. The statistician will be blinded to both groups during data analyses. Intention-to-treat analysis will be performed for the primary and secondary outcomes. If necessary, a multiple imputation technique will be used to handle missing data. All analyses will be performed with JASP (version 0.11.1; JASP Team (2019), University of Amsterdam, the Netherlands) and with statistical software R Core Team (2019) for Mac and WRS2 package (108).

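### The article refers to primary outcomes but names none, and tests about 36 outcomes each at 0.05 with no control across them, so a false-positive finding is likely

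*Protocol article*

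**What the plan says.** All of the following is in the protocol article.

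- **Hierarchy.** Statistical Procedures says "Intention-to-treat analysis will be performed for the primary and secondary outcomes". No other section calls any outcome primary or secondary.
- **Tests.** The same section says "the effectiveness of different training programs on quantitative dependent variables will be assessed by a 2 × 2 mixed ANOVA". The factors are group and improvement (10 weeks from baseline, 6 months from baseline), plus their interaction.
- **Error rate.** "Significance level will be set at α= 0.05". It is not divided among outcomes.
- **Correction.** "Whenever a significant main effect or interaction will be observed", a Bonferroni "correction will be used to aid interpretation of these main effects or interactions". It therefore operates after a significant result and inside the ANOVA of one outcome.
- **Outcomes.** Table 1 and the outcome subsections list fitness, velocity and power, body composition, blood and activity measures, with no ranking.
- **Sample size.** The paragraph below Figure 1 takes d = 0.70 "based on a study of WB-EMS training on hip circumference in postmenopausal women". It assumes two groups, three time levels, alpha 0.05 and power 0.80, and arrives at 22 participants, or 14 per arm after a 25% dropout allowance.

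**The concern.** The analysis depends on a distinction between primary and secondary outcomes that the article never makes. In its place is a rule that treats every quantitative outcome alike: one ANOVA, 0.05, and no adjustment between outcomes. Within each ANOVA, two of the three F tests bear on the arms (group, and group by improvement), and the article does not say which one answers the trial question.

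Two things are at stake. First, if WB-EMS has no added effect, some outcome may well reach significance by chance and be reported as an effect. A null result is a realistic prospect here, because the Discussion bases its expectations for fitness on earlier studies in which WB-EMS was not superior to other training. Second, with no outcome fixed in advance, the article gives no way to tell a confirmatory result from one picked out of a long list. The sample-size variable does not settle this: hip perimeter is one of twelve body-composition items and is given no priority.

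**Working it through.** **1. The plan's own figure.** The article states no family-wise error rate; its only related figure is N = 22. For a within-between interaction with f = d/2 = 0.35, 2 groups, m = 3 times and sphericity, λ = N f² m / (1 − ρ). The correlation ρ between repeated measures is not stated. Assuming ρ = 0.25:

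- N = 22: λ = 22 × 0.1225 × 3 / 0.75 = 10.78 on 2 and 40 df, power 0.815.
- N = 20: power 0.771, so 22 is the smallest even total.
- N = 28: detectable d = 0.604, against the stated 0.60.

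Both stated figures are reproduced, but only for a two-group by three-time interaction.

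**2. Counting outcomes.**

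| Domain | Main count | As in Table 1 | Widest |
|---|---|---|---|
| EXERNET ("consisting of 8 tests modified and previously adapted from" existing batteries) | 8 | 8 | 11 (three tests done on both sides) |
| Progressive resistance test ("the mean velocity and the mean power of exertion will be assessed in this study") | 4 (squat and bench press) | 2 | 4 |
| Body composition | 11 (height left out) | 12 | 13 (height and muscle mass) |
| Blood | 9 | 7 | 9 |
| IPAQ-E | 4 | 3 | 4 |
| **Total** | **36** | **32** | **41** |

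The two outer columns include height; without it they are 31 and 40.

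**3. Expected false positives, with no true effect on any outcome.** One group test per outcome: 36 × 0.05 = 1.8. Two arm-related tests per outcome: 72 × 0.05 = 3.6. Correlation does not change these expectations.

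**4. Chance of at least one false positive under independence, 1 − 0.95^k.**

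- k = 32: 80.6%
- k = 36: 84.2%
- k = 41: 87.8%
- k = 72 (group and interaction for 36 outcomes): 97.5%

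Counting only results that favour WB-EMS, one test per outcome: 1 − 0.975^36 = 59.8%.

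**5. The same chance with correlated outcomes.** Simulation of 200,000 draws of normal test statistics, 36 outcomes. The article gives no correlations, so all values are assumptions. In the two-test column, the group and interaction statistics are taken as independent of each other.

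| Correlation structure | One test per outcome | Two tests per outcome |
|---|---|---|
| Within the five domains 0.3, between 0 | 80% | 96% |
| Within 0.5, between 0 | 73% | 93% |
| Within 0.5, between 0.1 | 72% | 92% |
| Within 0.7, between 0.1 | 61% | 85% |
| All outcomes share 0.2 | 78% | 95% |
| All outcomes share 0.3 | 72% | 92% |
| All outcomes share 0.5 | 55% | 80% |
| All outcomes share 0.7 | 36% | 59% |

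**6. Would hip perimeter at 10 weeks inherit the stated power?** Two-sample t test, two-sided 0.05, d = 0.70 read as the standardised difference in that comparison, no covariate adjustment. The noncentrality is d√(n/2).

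- 11 per arm: 0.70 × √5.5 = 1.64 on 20 df, power 35%.
- 14 per arm: 0.70 × √7 = 1.85 on 26 df, power 43%.
- 80% power needs 34 per arm.

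So it would not.

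**The case against.** **A false positive is almost certain.** A reader might infer this from the 97.5% figure. The documents do not support it. The figure needs two tests per outcome and full independence, and the article itself rules independence out: BMI is calculated from weight and height, and total activity is the sum of the three activity scores. This part of the objection stands, and likely is the right word.

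**The count is soft.** Table 1 is shorter than the text for blood and activity, and some measures have another stated role. IPAQ-E is also a control tool for activity between post-test and follow-up, creatine kinase is described as a marker of muscle damage, and sodium and potassium as a check of osmotic balance. This is fair, but its effect is moderate: removing all four IPAQ-E scores still leaves 32, and the Discussion plans to analyse IPAQ as an outcome anyway.

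**The trial has no primary outcome at all.** A reader might infer this too, but the article cannot show it. The trial is registered, and the wording of the intention-to-treat sentence may point to a designation in the registry, which is not at hand. The finding is therefore limited to this article.

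**This is detail that a condensed article leaves out.** That defence does not hold. The article gives an outcomes section, a sample-size basis and an error rule, and it relies on the primary/secondary distinction itself.

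**Hip circumference is the primary outcome by implication.** The text uses it only as the source of an effect size. The stated objective is physical condition and health, and the Discussion cites earlier studies that found no group differences in anthropometric measures.

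**The statistician is blinded.** This limits selection in favour of one arm but does not control error across outcomes.

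**Conclusion.** The point holds in measured form. The article invokes an outcome hierarchy that it does not define, and its testing rule, followed as written, controls error only within each outcome. If WB-EMS has no effect on any outcome, at least one false-positive group effect is likely. The most plausible range is roughly 60% to 80%; the ceiling for one test per outcome is 84%, and even the most heavily correlated case examined gives about seven times the nominal 5% (36 / 5 = 7.2). Reading interactions as arm differences as well raises every one of these figures.

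The percentages rest on a count of 36, on assumed correlations and on a complete null. The expected 1.8 false-positive group effects need only the count and the null. That the article names no primary outcome, time point or contrast rests on no assumption.

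**What to change.** Before unblinding:

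1. In Statistical Procedures and in the registry, name one primary outcome, one time point and one between-arm contrast, tested at two-sided 0.05. Keep this consistent with any designation the registry already holds.
2. Declare every other outcome either secondary, with Holm or false-discovery control within each family (fitness, strength, body composition, blood, activity), or exploratory, with estimates and confidence intervals and no significance claims.
3. Restate the power or the detectable effect in the sample-size paragraph for the chosen outcome and contrast. This is needed even if hip perimeter at 10 weeks is chosen, because the stated 80% was computed for a different test.

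With one pre-stated primary test, the type I error of the trial's main claim is 5%. Keeping all 36 outcomes on an equal footing would instead need 0.05 / 36 = 0.0014 per outcome under Bonferroni.

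The cost is an amendment to the registry entry and the analysis plan, and the loss of nominal significance claims for secondary outcomes. No new data are needed. The restated power may be well below 80% at the planned size, and the report should say so.

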## Discussion

The worldwide implementation of effective protocols to study the WB-EMS's effects is limited. However, it is a much-extended training methodology which is being used by thousands of people without a specific legislative control and an adequate official instructional guide for health professionals. Therefore, the present study aims to enhance the knowledge of the body's responses within this training methodology. The aim is to analyze the effect of a training program with WB-EMS on the physical condition and health of postmenopausal women. To do so, we will carry out an intervention based on the development of the physical condition through the implementation of the WB-EMS. This will allow us to carry out a subsequent multivariable analysis of the effects of this program, through evaluation techniques of different kinds. We will proceed with the analysis of blood parameters to observe the evolution of endocrine and metabolic aspects. We will carry out a physical performance test as a way to observe the differences in physical condition. With an anthropometric analysis, we will study changes in body composition and with the IPAQ we will analyze the adherence to physical exercise generated by the intervention in the participants by comparing the total activity in the week before the intervention and the total activity in the week before the follow-up. This variety of techniques for assessing physical fitness has the purpose of approaching the problem from various perspectives, which becomes the main contribution with respect to the previous literature.

To verify the effectiveness of WB-EMS, it is essential the isolation of its effects from the ones produced by voluntary contraction. In some of the previous studies, the control group received an intervention that was not equivalent to the one applied in the experimental group (58, 109–112). This procedure prevents the analysis of the WB-EMS's effect by itself. In other studies, the control group did not receive any type of intervention (64, 113), which prevents comparability between treatments. Another study compared two different types of training with WB-EMS, which only allowed the comparison of one treatment with another but prevents the analysis of the effect of the WB-EMS by itself (66). Other studies designed interventions whose control group carried out exercises of the same nature as the experimental group, but their training did not match the volume and frequency of training loads (58, 60, 114, 115). The protocol of the present study intends to carry out an experimental phase in which the interventions of both groups are completely comparable in terms of type of movements and training volume (116–118). It will allow identifying precisely the isolated effect of the WB-EMS.

The expected effects of our WB-EMS application protocol related to the development of physical fitness are based on those found by (112) when carrying out a 12-weeks training program with sedentary men. The authors observed that, except for slight improvements in some physical variables, the changes caused by the WB-EMS training were not superior to those of other exercise programs. Similar results were found by (116) in physically active women. The authors concluded that after 4 weeks of intervention, the WB-EMS training could serve as a reasonable but not superior alternative to classic training regimes. On the basis of this finding, it could be considered that the WB-EMS could be an adequate methodology to guarantee the training intensity necessary to cause positive adaptations in the organism. While it does appear to be as effective as other methodologies such as high-intensity interval training (HIIT), WB-EMS could be a good tool in order to reach the intended training intensity with the absence of abrupt movements and high resistance loads. Thus, it would be an adequate approach to postmenopausal women's physical training.

In Filipovic et al. (119), Kemmler et al. (58), and Wirtz et al. (118) the effects of WB-EMS on anthropometric parameters were analyzed without finding significant differences between the experimental group and the control group. Regarding the analysis of blood parameters, it could appear that there was some kind of significant improvement in cholesterol levels, as it happens in (109). Due to this, given the results obtained to date, the fact of finding significant changes in the blood parameters of the present study would be possible. In Kemmler et al. (113) no changes in triglycerides, glucose and cholesterol were observed after 26 weeks of training with WB-EMS. Similar results were noted in (80) given that no differences were noted in the analysis of the evolution of testosterone, cortisol, and growth hormone.

The way in which the health professional approaches the proposal of the physical activity program to which the patient is intended to adhere seems to be of great importance. It is necessary to assess correctly the needs of the person to propose appropriate exercise to their characteristics. It will also be crucial for the health professional to know how to clearly convey the need to adopt a healthy lifestyle and plan a good methodology and guidelines that will have to be followed to achieve it (120). To comply with this methodology, this study will hold theoretical lectures in which participants will be informed about the type of physical exercise they will perform during the study. They will be explained in detail the training program that we will carry out with them as well as the benefits it will entail for their health and their quality of life. It has been established that technology-based exercise programs have good adherence and may provide a sustainable means of promoting physical activity and preventing falls in older people (121). Taking these results into account, we hope to obtain satisfactory adherence to physical activity with the sample of this study.

Some advantages and limitations of this protocol deserve comments. On one hand, as the main advantage, we should mention that it ensures the assessment of the isolated WB-EMS's effects. Besides, by carrying out this multivariate assessment it is possible to evaluate postmenopausal physical fitness from various perspectives. It can be said that the study will allow other clinicians to use a more structured guide to get reproducible results. On the other hand, as limitations, it must be pointed out that the selection of the participants is carried out from a voluntary population from a big sports center. This procedure could derivate in a selection bias. This must be considered in the generalization of the results to other health systems.

In summary, this trial will provide insight into the effect of WB-EMS in postmenopausal women, after a 10-weeks intervention. Practitioners, exercise therapists, and instructors will be provided with a feasible, validated WB-EMS training program whose effect on physical fitness and health is scientifically assessed. Finally, the results of the current trial may help to develop further theories and models explaining WB-EMS training effects in general and particularly with older adults.

## Ethics Statement

The protocol of this study has been approved by the ethical committee of the Arnau of Vilanova's University Hospital, Lérida, (Spain). Project reference: CEIC-1701. All participants will be informed of the details of the study and will sign an informed consent form before starting the investigation.

